### Intervention

Participants in both groups will continue with their on-going medical care To measure the true effect of the knitting intervention, active hand exercises need to be avoided since they are proven effective for HOA [7, 9–16, 61]. This may not be possible thus all participants will complete a daily activity log.

Participants in **Group 1** will take part in a low-intensity knitting program, performed as a morning functional activity, which will comprise two components: 1) bi-weekly 20-min knitting sessions at a senior’s club and 2) 20-min home daily knitting sessions for the five remaining weekdays over 12 consecutive weeks (total of 90 sessions). The bi-weekly 20-min knitting session will take place, at **a Senior’s Club in metropolitan Ottawa,** on Tuesday and Thursday mornings with a group of regular members who knit wool blankets for sick children admitted CHEO, a regional Children’s Hospital. The blankets are composed of individual squares that are assembled together. Each wool square takes approximately 20 min for a beginner knitter. Each knitter will be encouraged to knit one wool square per day for a total of seven squares per week. To avoid excessive isometric strength and potential muscle fatigue with the use of small needles that require precise pinching, participants will use specific knitting needle and wool sizes (sizes #6 and #5 respectively according to the Standard Yarn Weight System (**http://www.craftyarncouncil.com/weight.html**). Study participants will learn how to knit with a qualified instructor from Senior’s Club during the knitting sessions which will also be supervised by a trained OT to ensure that the physiological and clinical characteristics of therapeutic exercise are being met. A knitting instructor will ensure that participants follow the prescribed program and if their individual logbooks, where they recorded their daily hand activities and morning stiffness and pain levels, are filled properly. In the event that a session is missed, participants in Group 1 will receive a telephone reminder from the research assistant to encourage them to attend the next session. At the end of 12 weeks, participants will be encouraged to continue on with the program if they gained an improvement of their condition.

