### Self-reported and performance-based clinical outcomes outcome measures (Table 1)

The clinical outcomes were selected according to the OMERACT framework illustrated in Fig. 2 and include the followings:

**Table 1 Tab1:** Assessment schedule for primary, and secondary outcome measures

Assessment	Admission	Daily	Baseline	3/6/9 weeks mid intervention	12 weeks end of intervention	4 weeks follow-up
Informed consent (pre-admission)	X					
Diagnosis of HOA based on ACR criteria	X					
Socio-demographics	X					
Edinburgh Handedness Inventory	X					
Self-reported daily morning stiffness intensity (Visual analogue scale: VAS) (primary daily outcome)	X	X	X	X	X	X
Self-reported daily pain intensity (VAS) (intermediate daily outcome)	X	X	X	X	X	X
Pain intensity (Auscan) (periodic secondary measurement)			X	X	X	X
Morning stiffness severity (Auscan) (periodic secondary outcome)			X	X	X	X
Hand functional status/difficulty in activities of daily living (Auscan) (periodic secondary outcome)			X	X	X	X
Disease activity status (periodic secondary outcome)			X	X	X	X
Dynamometric strength measurements (Grip and pinch measurements) (periodic secondary outcome)			X	X	X	X
The Functional Index for Hand Osteoarthritis (FIHOA) (periodic secondary outcome)			X	X	X	X
Hand physical activity level (periodic secondary outcome)		X	X	X	X	X
Patient global assessment (periodic secondary outcome)			X	X	X	X
Quality of life (EQ-5D) (periodic secondary outcome)			X	X	X	X
Self-efficacy (periodic secondary outcome)			X	X	X	X
Physical Activity Enjoyment Scale (PACES) (Group 1 only)				X	X	X
Adherence to knitting program (Daily secondary outcome)			X	X	X	X
7-day Physical Activity Recall (PAR) (Daily secondary outcome)			X	X	X	X

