### Self-reported clinical outcomes (Table 1)

**Morning stiffness and pain relief**, using daily visual analogue scale for morning stiffness (primary outcome) and for pain (secondary outcome) will be recorded before (baseline) and after knitting (immediately, 2 h and 4 hours after the 20-min knitting daily morning activity). Daily morning stiffness after 2 h knitting daily morning activity will be our primary outcome measure of this protocol. This choice of primary and intermediate outcomes is based on the feasibility study conducted by the team.

**Functional status**, using Australian/Canadian Osteoarthritis Hand Index (AUSCAN) tool as a validated, reliable and responsive measurement scale for HOA [62–64] was adopted. The AUSCAN includes a 15-item scale, with items grouped into three sub-sections: A) pain intensity, B) stiffness severity and C) hand functional status/difficulty in activities of daily living. It uses a five-point scoring system. A score of 0 represents no pain or no severity in stiffness or no difficulty in performing functional tasks; scores between one and four represent mild to extreme gradations, respectively. Morning stiffness and hand functional status are included in the AUSCAN.

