**Hand activity**
***level***, using an adapted 7-Day Physical Activity Readiness (PAR) [65–67] was used. The 7-day PAR is a validated instrument in a calendar format in which a participant can indicate the PA duration (minutes per day) and PA frequency (days per week). An adapted version of the 7-day PAR will be included in the logbooks where physical activity is split into distinct Knitting and other hand activities categories. The logbooks will also include a daily visual analogue scale for morning stiffness and pain intensity before and after knitting, information about hand physical activity level and knitting technique as well as a weekly questionnaire on actual changes in PA, medication intake (not encouraged), habits and adverse events. A similar logbook was created for PA activity other than knitting recording for the participants in the control group 2. ***Patient global assessment*** will be evaluated by asking patients if their condition after knitting program “fully improved”, “partially improved”, “did not improve” or “was worse compared to the beginning of the study” [31]. ***Health-related QoL*** will be assessed using the EuroQoL Index (EQ-5D-5 L) [68] including mobility, self-care, usual activities, pain/discomfort and anxiety/depression subscales.

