### Implementation outcomes

The following implementation outcomes are not represented in the OMERACT framework (fig. 2). ***Self-efficacy*** will be assessed using The Stanford Arthritis Self-Efficacy Scale (ASES) [33], a ten-point scale ranging from one (very uncertain) to 10 (very certain). Level of ***knitting enjoyment*** will be measured using Physical Activity Enjoyment Scale (PACES) for participant in group 1 only [70]. ***Adherence to PA/knitting program*** will be estimated as the number of knitting sessions attended at the Club and performed at home divided by the number of knitting sessions prescribed (84 sessions), as recorded in the participants’ logbooks, using the 7-Day PAR calendar [65] as well as attendance at the senior’s club. The number of wool squares that were knitted will be also reported in the participants’ logbooks. However, knitting technique will be recorded how the participants hold the stabilizing and mobile needle and which hand is used by the trained OT. Adverse events observed will be also compiled. All these clinical and implementation outcomes measures were pilot tested [43].

Please insert Table 1 Assessment schedule for primary, and secondary outcome measures.

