### Statistical analysis

Descriptive statistics will be used to summarize the study variables and to assess the distributional assumptions of the statistical techniques used. An intention to treat analysis will be conducted for all the data analyses.

A per protocol analysis will be considered as part of the sensitivity analyses. The primary outcome is the area under the curve (AUC) at 2 h for stiffness. That is, stiffness at 2 h post-awakening from sleep will be assessed each day for 12 weeks, and the AUC over this 12 week period will then be calculated. Similar AUCs will be calculated for stiffness at 0 h (at awakening), 4 h (post-awakening) and evening. Also, similar AUCs for the secondary outcomes pain and function will be calculated.

For the primary outcome (AUC at 2 h for stiffness) participants in the knitting group will be compared to participants in the control group using independent Student’s t-test with the pooled or separate variance estimate as appropriate. For the primary and secondary outcomes, the area under the curve (AUC) for stiffness, pain and function will be compared using a 2-way analysis of variance (ANOVA) with the between factor group (knitting vs control) and within factor time (0 h, 2 h, 4 h, evening). Tukey’s [71] honest significance difference (HSD) will be used to make specific pairwise comparisons. The secondary outcomes, AUSCAN overall, AUSCAN pain, AUSCAN stiffness, AUSCAN function, hand and fingers strength and physical function, self-efficacy, hand physical activity level and adherence, global patient improvement as well as QoL will be compared using a 2-way analysis of variance (ANOVA) with the between factor group (knitting vs control) and within factor time (baseline, 3 wk., 6 wk., 9 wk., 12 wk. and 4-wk Follow-Up). Again, Tukey’s HSD [71] will be used to make specific pairwise comparisons. As a secondary analysis, additional time assessments to 16 weeks will be included in the above analyses to assess follow-up. An alpha significance of 0.05 was chosen for all analyses. Mixed models repeated measured will be used to accommodate missing data. No interim efficacy or subgroup analyses are planned.

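### Two planned secondary ANOVAs, function by time of day and adherence between arms, do not match the data the protocol collects

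*Protocol article*

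**What the plan says.** All references are to the protocol article.

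**Within-day ANOVA.** Statistical analysis says that "the area under the curve (AUC) for stiffness, pain and function will be compared using a 2-way analysis of variance (ANOVA". The between factor is group and the repeated factor is "within factor time (0 h, 2 h, 4 h, evening".

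**Function measures.** Table 1 lists "Hand functional status/difficulty in activities of daily living (Auscan) (periodic secondary outcome" with marks at baseline, 3/6/9 weeks, 12 weeks and follow-up, and none under Daily. FIHOA has the same pattern. Self-reported clinical outcomes (paragraph on hand activity level) gives the logbook's daily visual analogue scales as morning stiffness and pain.

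**Daily readings.** Self-reported clinical outcomes says that stiffness and pain "will be recorded before (baseline) and after knitting (immediately, 2 h and 4 hours after the 20-min knitting daily morning activity".

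**Visit-level ANOVA.** Statistical analysis adds that "hand physical activity level and adherence, global patient improvement as well as QoL will be compared using a 2-way analysis of variance", knitting against control, at six times from baseline to the 4-week follow-up.

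**Adherence.** Implementation outcomes defines it as sessions attended at the club and done at home, "divided by the number of knitting sessions prescribed (84 sessions". Intervention describes the program as running "over 12 consecutive weeks (total of 90 sessions".

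**Patient global assessment.** It "will be evaluated by asking patients if their condition after knitting program" improved fully, partially or not at all, or was worse than at the start of the study. Table 1 marks it at baseline and at every later visit, with no restriction to one group.

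**The concern.** An analysis can be run only on data that the schedule produces, and a between-group comparison is informative only if the outcome is defined in both groups. Two of the listed secondary analyses fail one of these tests.

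The function AUC by time of day needs function scores at four times each day, and nothing in the article describes one. The adherence comparison sets the knitters' attendance against a group that was given no sessions to attend.

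The second failure carries the larger interpretive risk. The Background lists adherence among the outcomes to be compared with the waiting list, and the general hypothesis expects improvement in every daily clinical and implementation outcome. A significant group effect on adherence would be nearly certain and could be counted as support, although it shows only that people assigned to knit did so more than people who were not.

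**Working it through.** The check sets each planned ANOVA against the collection schedule. The only arithmetic is cell counting and the session total.

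**1. Function by time of day**

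- Design: 2 groups × 4 times (0 h, 2 h, 4 h, evening) = 8 cells.
- Function sources: AUSCAN function and FIHOA, both at visits only (Table 1).
- Daily scales: stiffness and pain only (Self-reported clinical outcomes).
- Cells with data: 0 of 8.

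Hand physical activity level does have a Daily mark in Table 1. It records minutes and days of activity, however, not function, and it is not tied to times of day. The mixed models named for missing data do not help either, because an outcome measured at no level of the factor is not a missing observation.

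**2. Adherence, knitting against control, from baseline**

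- Design: 2 groups × 6 times (baseline, 3, 6, 9 and 12 weeks, follow-up) = 12 cells.
- Control: no sessions prescribed. The group is barred from the club sessions, and its logbook records activity other than knitting. This removes 6 cells.
- Group 1 at baseline: no session has yet been prescribed. This removes 1 cell.
- Group 1 at follow-up: the 12-week program has ended, and continuing is only encouraged for those who improved. This removes 1 cell.
- Cells with a meaningful value: 12 − 6 − 1 − 1 = 4 (Group 1 at 3, 6, 9 and 12 weeks).

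If a control's denominator is the number of sessions prescribed to that person, the value is 0/0. If it is fixed at 84, the value is 0/84 = 0 by design, and the group difference equals Group 1's own mean adherence: mean − 0 = mean. Neither version estimates a treatment effect. PACES, which also has no meaning for controls, is marked in Table 1 as Group 1 only; adherence is not.

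**3. Three items that contradict each other**

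| Item | One place | Another place |
|---|---|---|
| Evening level | Statistical analysis uses 0 h, 2 h, 4 h and evening | Self-reported clinical outcomes lists before, immediately after, 2 h and 4 h after knitting |
| Global assessment | Table 1 and the ANOVA include a baseline value, in both arms | The item rates change since study start and refers to the knitting program |
| Session total | Intervention: 90 | Implementation outcomes: 84 |

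Session total from the stated week: (2 club + 5 home) × 12 = 24 + 60 = 84, which is the adherence denominator. The difference is 90 − 84 = 6. A participant who completes all 84 would score 84/84 = 100%, or 84/90 = 93.3% if the other total were used.

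**The case against.** The strongest reply is that the article condenses a fuller protocol, and that its summaries of the logbook and questionnaires should not be read as complete. Taken item by item:

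- **Evening.** A reader might infer that no evening reading is collected. The article does not say so. It lists different reading times in two sections, and the logbook is not shown. This is a mismatch to reconcile. Even without an evening reading, the stiffness and pain ANOVAs can run on the remaining times. Whether those times count from awakening or from knitting is a separate question about the outcome definition and is not part of this point.
- **Global assessment.** A reader might infer that controls have no values. Table 1 does not restrict the item, and Measurement frequency schedules evaluations in both groups. The reference to the knitting program may also paraphrase the item. What stands is that a rating of change has no baseline value and that the described wording does not suit a waiting list.
- **Ordinal scale.** One might also demand an ordinal model for the four categories. That is largely a preference and is commonly settled in an analysis plan that is not shown, so it is not pressed.
- **Function.** An AUC across the AUSCAN visits could be calculated. That is true, and it means that only the time-of-day factor fails. The stated analysis still uses that factor.
- **Adherence.** The outcome is titled to cover physical activity as well as knitting, and controls keep an activity log. Activity data for controls therefore exist, but the stated ratio counts knitting sessions only.
- **84 and 90.** The adherence formula fixes 84, so the 93.3% scenario is not what the plan specifies. The conflict has no bearing on whether an ANOVA can be run.

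The replies narrow the point. They do not supply function scores by time of day or make adherence comparable between the arms.

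**Conclusion.** The point holds for two secondary analyses. The function AUC by time of day has no data in any of its 8 cells. The between-group adherence analysis is meaningful in 4 of 12 cells, all in Group 1, so its group effect is undefined or true by design. The evening level, the global assessment and the session totals are contradictions to reconcile.

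A reader might go further and conclude that most of the listed ANOVAs fail or that the main result is at risk. The documents do not support that. The primary t-test on the 2 h stiffness AUC needs no function, evening, adherence or global assessment data, and AUSCAN function already has its own visit-level analysis.

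The conclusion assumes that Table 1 and the outcome sections name every function measure, and that the adherence formula is the one to be analysed. If the full protocol holds a daily function scale recorded at those times, the first part falls away.

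**What to change.** 1. Remove function from the within-day ANOVA. Keep the visit-level analysis of AUSCAN function and physical function that is already planned.
2. Remove adherence from the knitting-against-control ANOVA. Report it descriptively in Group 1 over the 12-week program, and mark it in Table 1 as Group 1 only, without baseline and follow-up.
3. Either drop evening from the within-day factor or add an evening stiffness and pain scale to the logbooks of both arms.
4. Word the global assessment neutrally, as change since the start of the study, so that both arms can answer it. Remove its baseline mark and analyse post-baseline visits only.
5. Reconcile the session totals in Intervention and Implementation outcomes so that program and denominator agree. The stated week multiplies out to 84; the investigators need to confirm what is intended.

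Items 1, 2 and 5 cost only wording. Item 4 costs one reworded question. Item 3 costs nothing if evening is dropped, or a short daily entry if it is kept. The new question wording and any evening scale should be settled before data collection, because neither can be recovered afterwards. Sample size and the primary analysis are unchanged.

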### Study design

The study is a single blind, two-arm RCT with a parallel group design to compare two study groups: 1) a knitting intervention (Group 1) and 2) a waiting list control group (Group 2). The intervention period will be 12 weeks plus a follow-up at 4 weeks post-intervention to measure the retention effect. Since this RCT involves a physical intervention (i.e. knitting program), the therapist, participants, and research coordinator administering the program will not be blinded. A blinded independent assessor will be trained to assess the participants though performance evaluation and self-reported questionnaires given at baseline, 3,6,9,12-week as well as at 4-week follow-up to reduce detection bias. With training and standard operating procedures, it is anticipated that any performance bias due to unblinding will be minimized. The study design flow chart is presented in Fig. 1. The study protocol is approved by the University of Ottawa Research Ethics Board (#H02–16-12).

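### Read literally, the follow-up rule turns the VAS AUC into a 16-week figure that is 75% on-programme time and cannot measure retention

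*Protocol article*

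**What the plan says.** All references are to the protocol article.

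- **Purpose of follow-up (Study design):** "The intervention period will be 12 weeks plus a follow-up at 4 weeks post-intervention to measure the retention effect". No outcome is named there.
- **AUC outcome (Statistical analysis):** "stiffness at 2 h post-awakening from sleep will be assessed each day for 12 weeks, and the AUC over this 12 week period" is then computed, giving one value per participant. Similar AUCs are planned for other times of day and for pain and function.
- **Primary test:** the two groups' 2 h stiffness AUCs are compared "using independent Student’s t-test with the pooled or separate variance estimate as appropriate".
- **AUC ANOVA:** stiffness, pain and function AUCs are compared by group, "within factor time (0 h, 2 h, 4 h, evening". These levels are times of day.
- **ANOVA of the periodic outcomes** (AUSCAN scores, strength, self-efficacy, quality of life and others): by group, "within factor time (baseline, 3 wk., 6 wk., 9 wk., 12 wk. and 4-wk Follow-Up". Here follow-up is a level of its own.
- **Follow-up rule, placed after all of these:** "As a secondary analysis, additional time assessments to 16 weeks will be included in the above analyses to assess follow-up".

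No AUC or contrast specific to weeks 13-16 is described. Table 1 marks the stiffness and pain VAS as daily and also at the 4-week follow-up. It does not say whether the daily diary runs through weeks 13-16.

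**The concern.** The rule sends data up to week 16 into the analyses already described. The ANOVA of periodic outcomes already contains the follow-up visit, so the sentence adds something new only for the AUC analyses. Those have nowhere to place a post-programme period: the t-test has no time factor, and the AUC ANOVA has only time of day. Applied as written, the rule lengthens the AUC.

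A 16-week AUC averages on-programme and post-programme days. It can differ between groups because of weeks 1-12 alone, so it does not answer whether an effect persists.

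The protocol itself treats absence of a lasting effect as a live possibility. The Strengths and limitations section justifies daily knitting by a symptom effect of about four hours, and the Conclusion says the trial might show a same-day effect only. In that case the pooled AUC would suggest persistence of the main symptom measure where there is none.

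**Working it through.** **Inputs from the protocol**
- Programme 12 weeks = 84 days; study 16 weeks = 112 days; post-programme 28 days (Study design; Strengths and limitations).
- Effect size 0.8, power 80%, alpha 0.05, 28 per group, 30 after 5% dropout (Sample size calculation). Sidedness is not stated; two-sided is assumed.

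**Assumptions that the protocol does not give**
- Effect exactly zero in weeks 13-16.
- Equal between-person SDs of the two period means.
- Within-person correlation r between the two period means, varied from 0.5 to 1.

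**Step 1: the plan's own figure.** For d = 0.8 and 80% power, the normal approximation gives 25 per group and the exact noncentral t gives 26. The stated 28 is close to this and has 83.6% power. Dropout: 28/0.95 = 29.5, rounded up to 30. The sample size is not in dispute and serves as the base for what follows.

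**Step 2: share of on-programme time.** 84/112 = 0.75. With no effect in weeks 13-16, the raw difference in the 16-week daily mean is 0.75 × (on-programme difference) + 0.25 × 0, which is 75% of the on-programme difference.

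**Step 3: standardised difference of the 16-week AUC.** In units of the period SD:

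SD16 = sqrt(0.75² + 0.25² + 2 × 0.75 × 0.25 × r) = sqrt(0.625 + 0.375r)

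d16 = 0.75 × 0.8 / SD16 = 0.60 / SD16

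**Step 4: chance of p < 0.05 with nothing retained** (two-sided t-test, noncentral t):

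| r | SD16 | d16 | 28 per group | 30 per group |
|---|---|---|---|---|
| 0.5 | 0.90 | 0.67 | 69% | 72% |
| 0.8 | 0.96 | 0.62 | 63% | 66% |
| 0.9 | 0.98 | 0.61 | 61% | 64% |
| 1.0 | 1.00 | 0.60 | 60% | 63% |

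**Step 5: simulation check.** With 20,000 simulated trials per setting at 28 per group, the 16-week AUC was significant in 69.2% (r = 0.5) and 61.4% (r = 0.9). A comparison of weeks 13-16 alone was significant in 4.8% and 4.9%, the nominal rate.

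**The case against.** **The pooled window is inferred.** The article never says that the AUC is extended to 112 days. The phrase about time assessments could echo the visit levels in the ANOVA sentence shortly before it, and the rule could simply be redundant. The article does repeat itself elsewhere: its dropout sentence appears twice in the sample size section. A separate AUC for weeks 13-16 may also have been meant. This stands in part. Pooling is the literal reading for the AUC outcomes but not the only one, so a reader should not infer that the investigators have definitely chosen it. No alternative is written down, however, and the AUC analyses have no factor that could hold one.

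**Retention is measured elsewhere.** This stands. The follow-up clause in the objectives (end of Background) covers strength, physical function, self-efficacy, hand activity and adherence, global improvement and quality of life, not the VAS AUC. Those outcomes, and AUSCAN stiffness and pain, are analysed with follow-up as a separate level and Tukey comparisons. A reader might infer that the trial's whole assessment of retention is compromised; the document does not support that.

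**Windowing is detail for an analysis plan.** This stands for interpolation. One might infer that a lone week-16 reading would be given many days' weight in a trapezoid, but the article specifies neither a trapezoid nor a single reading. It does not excuse a stated rule that, applied to the AUC, yields the wrong quantity. It is also no aggravation that a cumulative AUC keeps the full raw difference, because rescaling by a constant leaves d and p unchanged.

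**Weeks 13-16 are not free of knitting.** The Intervention section encourages participants who improved to continue. A separate window would therefore not isolate pure retention. This stands, and it limits how the result can be described, but it does not remove the pooling.

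**Conclusion.** The point holds for the secondary follow-up analysis of the AUC outcomes only. Taken literally, the rule produces a measure that is 75% on-programme time and cannot estimate the retention effect named in the Study design section. With the planned 0.8 SD effect on programme and none afterwards, that measure would show d of about 0.67 to 0.60 and be significant about 69% to 60% of the time at 28 per group, against about 5% for weeks 13-16 alone.

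The figures rest on the literal reading, the full planned effect, exactly zero effect after week 12, equal period SDs and r between 0.5 and 1. Other values change the size. The flaw itself follows from the 84/112 weighting and does not depend on them.

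The primary 12-week comparison is untouched, and so are the periodic outcomes.

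**What to change.** Keep the 12-week AUC and its analyses unchanged. Replace the follow-up sentence with a rule for the VAS AUC outcomes:

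- If the daily diary continues in both groups, compute each participant's mean daily VAS over days 85-112 and compare groups on that window alone.
- If it does not, compare groups on the week-16 VAS that Table 1 already schedules, and compute no 16-week AUC.

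State which of the two applies. Because improved participants are encouraged to continue the programme, describe the result as the group difference after the programme period, not as pure retention.

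**Cost:** one sentence and, if not already intended, four more weeks of a diary that participants already keep. No extra participants are needed. The estimate will be less precise than the pooled AUC, especially if it rests on the week-16 reading alone.
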